### Design

This study is a pragmatic randomized controlled trial (RCT) with two groups: intervention group (*n* = 334) and control group (*n* = 176). The subjects will be followed up to 12 months. The duration of the study is 3 years and is divided into three phases: phase I, intervention design and pilot study for 1 month; phase II, recruitment during 24 months; and phase III, analyses of the effectiveness of the intervention, publication of the results, and dissemination (6 months after phase II).

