**Fig. 3 Fig3:**
[figure not shown]
Strategy intervention in the intervention group. NRT nicotine replacement therapy

All patients in the intervention group will receive eight telephone calls during 1 year (48 h, 1 week, 15 days, and 1 , 3 , 6 , 9, and 12 months post discharge), regardless of whether they continue smoking or not. The intervention lasts for 12 months, unless the patient rejects to continue participating in the study. The intervention adapts its objectives depending on the smoking status of the patient in each call (see Fig. 3 in which the different strategies are explained according to the smoking status assessed in each call, whether he/she is abstinent or not, is willing to allocate a “D day”, takes NRT).

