### Data collection

A computer-specific application for the study will be designed for data recording and management, including randomization. The software will be created following the current standards of security, privacy, and confidentiality. All study researchers will have access to the application using a personal username and password. Clinicians from each center will only be able to register and have access to review information from patients from their own center. The 061 CatSalut Respon nurses will obtain data from patients registered in the five centers to do the telephone intervention. Collected data will be exclusively used to carry out the intervention (IG or CG), supervision, and evaluation. Patients will be informed about the application uses and purposes, the existence of their profile including their personal details, and the person responsible for their treatment, along with their access rights, rectification, cancellation, and opposition. Once the patient has given his/her consent, clinicians will input data from the basal interview into the application.

Once the study is completed, professionals from the hospitals and 061 CatSalut Respon will no longer have access to the database. The ICO is responsible for properly saving the files and its protection by encrypted secure systems, until its eventual destruction (5 years after study completion). The database will not identify patients in any way, creating an individual encrypted code. Data collected during the study will be included in a file registered by the Spanish Data Protection Agency.

The intervention and the computer application will be firstly piloted in the five participating centers for 1 month for its evaluation before starting the study, to assess the adequacy of the fieldwork circuit and make minor changes in the protocol, if necessary.

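### The stated 3-year calendar leaves no room for the last recruits' 12-month assessment, so the timing of the 12-month analysis and the total duration need to be reconciled

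*Protocol article*

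**What the plan says.** All references are to the protocol article.

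- **Total length (Design):** "The duration of the study is 3 years and is divided into three phases".
- **Phase I (Design):** "phase I, intervention design and pilot study for 1 month". The Data collection section adds that the pilot runs "for 1 month for its evaluation before starting the study", so it comes before recruitment and does not overlap it.
- **Phases II and III (Design):** "phase II, recruitment during 24 months; and phase III, analyses of the effectiveness of the intervention, publication of the results".
- **Timing of phase III (Design):** "publication of the results, and dissemination (6 months after phase II").
- **Follow-up (Design):** "The subjects will be followed up to 12 months".
- **Intervention length (Telephone-based intervention components, after Fig. 3):** "The intervention lasts for 12 months, unless the patient rejects to continue participating in the study".

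The Primary outcome measure section compares abstinence at 1, 6 and 12 months. The Sample size and randomization section sizes the trial on 20% against 5% abstinence at 12 months, with 20% loss to follow-up. None of the three phases is set aside for completing follow-up once recruitment closes.

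**The concern.** The calendar and the follow-up are both stated, and they disagree. This is therefore more than a detail left to a fuller document. The assessment affected is the one the sample size uses, and the article presents its 1-year follow-up as the trial's novelty.

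If the project were run to the calendar, the latest recruits would not yet be due for their 12-month assessment when the analysis is done. The 20% allowance is for people lost to follow-up, not for people whose assessment has not come round. The article does not say how such participants would be handled. Leaving them out would make the 12-month result describe earlier recruits only. Counting them as smokers would shrink the difference between the groups. The Data collection section also ends hospital and quitline staff's database access when the study is completed. If completion meant month 36, that could come before the last calls and carbon monoxide checks.

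**Working it through.** **1. The plan's own figure.** The stated total is 3 years = 36 months. If the 6 months of phase III are a length, the phases sum to 1 + 24 + 6 = 31 months, which does not reproduce 36. If they are a start time, phase III begins at month 1 + 24 + 6 = 31 and can run to month 36, which agrees with 3 years. So the 31-against-36 mismatch depends on the reading. Step 2 does not.

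**2. Last 12-month assessment.** Last entry = 1 + 24 = month 25. Last assessment = 25 + 12 = month 37. That is 1 month after the stated end and 6 months after month 31, at which phase III either begins or ends.

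**3. Other readings of the calendar.**
- Pilot outside the 3 years: last entry at month 24 and last assessment at 24 + 12 = month 36. No month is left for analysis, and phase III would still be placed at month 30.
- Intervention design takes 5 unstated months, so that 6 + 24 + 6 = 36: last entry at month 30 and last assessment at month 42.

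No reading of the three phases as written gives every recruit 12 months and also leaves room for phase III.

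**4. Share not yet due.** Assume even accrual over months 1 to 25 (not stated in the article) and a data cut at month L. A participant has 12 months of follow-up only if entered by month L − 12, so

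share not yet due = [25 − (L − 12)] / 24.

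| Data cut L | Share | Of 501 | Of 510 |
|---|---|---|---|
| 31 | 6/24 = 25% | about 125 | about 127 |
| 36 | 1/24 = 4% | about 21 | about 21 |
| 37 | 0 | 0 | 0 |

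Two totals are shown because Sample size and randomization gives 334 + 167 = 501, while Design gives 334 + 176 = 510. The percentages do not change.

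**5. Effect on power at a month-31 cut.** Inputs: 334/167, 20% against 5%, two-sided α = 0.05 (sides are not stated in the article), 20% loss plus 25% not yet due. Fraction with a 12-month result = 0.80 × 0.75 = 0.60. With n₁ control, n₂ intervention, difference d and pooled proportion p̄ = (n₁p₁ + n₂p₂)/(n₁ + n₂):

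power = Φ[(d − 1.96·SE₀)/SE₁], where SE₀² = p̄(1 − p̄)(1/n₁ + 1/n₂) and SE₁² = p₁(1 − p₁)/n₁ + p₂(1 − p₂)/n₂.

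- *Those without a result excluded:* n₁ = 100.2, n₂ = 200.4, p̄ = 0.15, SE₀ = 0.0437, SE₁ = 0.0357. Power = Φ[(0.15 − 0.0856)/0.0357] = Φ(1.80) = about 96%.
- *All counted as smokers:* rates become 0.60 × 20% = 12% and 0.60 × 5% = 3%, with n₁ = 167, n₂ = 334, p̄ = 0.09, SE₀ = 0.0271, SE₁ = 0.0221. Power = Φ[(0.09 − 0.0532)/0.0221] = Φ(1.66) = about 95%.

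Both exceed the planned 90%. In the second case the difference falls to 12 − 3 = 9 points. The planned 20% loss alone, counted the same way, would give 16 − 4 = 12 points.

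**6. Duration that would fit.** Pilot + recruitment + follow-up of the last recruit + analysis = 1 + 24 + 12 + 6 = 43 months, which is 43 − 36 = 7 more than stated.

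**The case against.** The strongest reply is that nothing in the article ends follow-up on a calendar date. The termination criteria under Ethical considerations are completion of the procedures, withdrawal, and repeated failure to locate the patient. Every intervention patient is promised calls through 12 months, and the 12-month comparison is stated in several places. On this view the project timeline would slip and follow-up would not be cut short. The exact time of database lock is also something a condensed article may leave to the full protocol.

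Much of this stands. It rules out some stronger conclusions that a reader might draw:

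- *That late recruits will be dropped or counted as smokers.* No section says so. Either handling is an assumption.
- *That half the sample would lack the outcome.* This needs the 12-month analysis to be cut at month 25, the moment recruitment closes. If phase III starts 6 months later, that case is excluded. If phase III lasts 6 months, the analysis need only be finished by month 31.
- *That power would be lost.* Step 5 shows it stays above target at a month-31 cut.

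The reply does not remove the contradiction. The 3-year total and the position of phase III are stated figures that the design cannot meet, and waiting for the last visit is not stated. The one reading that would resolve it, with the 24 months covering recruitment and follow-up together, goes against the text, which gives all 24 months to recruitment.

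**Conclusion.** The point holds as an inconsistency between the stated calendar and the stated follow-up. The last 12-month assessment falls at month 37, or at month 36 with no analysis time if the pilot is outside the 3 years. This part rests only on figures in the article.

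The consequence is conditional. If the calendar were followed over the follow-up rules, and accrual were even, about 25% of participants would lack the 12-month outcome at a month-31 cut and about 4% at month 36. The 25% would come on top of the planned 20% loss. The harm would be incomplete 12-month data and possible bias. Power of about 95-96% means that sample size is not the issue. The documents do not support reading this as a plan to truncate follow-up. They support only that the plan does not rule it out, and that its dates need correcting.

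**What to change.** 1. State that the 12-month comparison is analysed only after the last participant's 12-month assessment.
2. Restate the duration to match. Keeping 24 months of recruitment and a 6-month analysis phase gives about 43 months. Say whether the pilot counts within the total, and whether the 6 months of phase III are a length or a start time.
3. If the 24 months were meant to include follow-up, say so and give the recruitment period separately.

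The cost is a change of wording and a stated duration about 7 months longer. No extra participants are needed.

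Keeping 36 months by recruiting for only 36 − 1 − 12 − 6 = 17 months is a feasibility trade-off and not a free alternative. From the article's 1744 admissions a year and 70% smokers, it would need 501 / (1744 × 0.70 × 17/12) = 501/1729 = 29% of expected smokers, against 501/2442 = 21% over 24 months. Both percentages are before the eligibility exclusions, so uptake among eligible patients would have to be higher.

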### Study population

The study population includes smokers with mental disorders admitted to the mental health wards of five acute care hospitals of Barcelona (Hospital Clinic i Provincial de Barcelona, Hospital de la Santa Creu i Sant Pau, Hospital Universitari Vall d’Hebron, Hospital Universitari de Bellvitge, and Hospital Hestia Duran i Reynals). The inclusion criteria are: patients who consider themselves smokers, both daily and occasional smokers (less than 1 cigarette per day); adults of both sexes aged 18–76 years; patients who have stayed in an acute or detoxification mental health unit for more than 24 h; patients with a telephone, fixed or mobile; residents in the metropolitan area of Barcelona; and patients who provide informed consent. The exclusion criteria are: patients discharged from the psychiatric emergency rooms; patients with dementia or brain damage; patients who do not speak or read Spanish or Catalan; pregnant women; patients with hearing and/or speech deficit; patients who are trying to quit smoking in another center or using another intervention; patients who have voluntarily requested discharge; patients who are discharged to another inpatient unit; and patients who plan to move their household outside the Barcelona metropolitan area within the next 24 months.

Clinical professionals (coordinated by a researcher from each hospital) will evaluate whether patients met the inclusion/exclusion criteria.

### Sample size and randomization

Data from the five centers indicate that each year 1744 patients are admitted to their acute and detoxification mental health units, of which 70% are expected to be smokers [5]. Setting a risk of α = 0.05 and β = 0.10, and with 2:1 randomization, 334 subjects are required in the IG arm and 167 in the CG arm to detect a statistically significant difference of 15 percentage points between the proportion of abstinence in both groups (IG abstinence rate, 20% and CG abstinence rate, 5%) after 12 months, with an estimated 20% loss to follow-up. Hence, participants will be randomized into the IG and the CG with 2:1 allocation using mapping software. The main reason for the unequal allocation (2 IG:1 CG) was ethical, in order to maximize the number of participants included in the treatment group, as the treatment is supposed to be beneficial for them.

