**Methods:**

A pragmatic randomized controlled trial, single blinded, will include 2:1 allocation to the intervention group (IG) and the control group (CG). The IG will receive telephone assistance to quit smoking (including psychological and psychoeducational support, and pharmacological treatment advice if required) proactively for 12 months, and the CG will receive only brief advice after discharge. The sample size, calculated with an expected difference of 15 points on smoking abstinence between groups (IG, 20% and CG, 5%), α = 0.05, β = 0.10, and 20% loss, will be 334 participants (IG) and 176 participants (CG). Participants are adult smokers discharged from psychiatric units of five acute hospitals.

Measurements include dependent variables (self-reported 7-day point prevalence smoking abstinence (carbon monoxide verified), duration of abstinence, number of quit attempts, motivation, and self-efficacy to quit) and independent variables (age, sex, and psychiatric diagnoses). In data analysis, IG and CG data will be compared at 48 h and 1, 6, and 12 months post discharge. Multivariate logistic regression (odds ratio; 95% confidence interval) of dependent variables adjusted for potential confounding variables will be performed. The number needed to treat to achieve one abstinence outcome will be calculated. We will compare the abstinence rate of enrolled patients between groups.

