There are several potential limitations. In Catalonia, Spain, patients who have high motivation to quit smoking at the time of discharge from acute mental health hospitals are referred to a face-to-face intensive smoking cessation intervention with free pharmacotherapy for smoking cessation. These patients are excluded from our study and, therefore, our sample does not include patients with high motivation to quit smoking. Nonetheless, we will assess all patients who meet the study inclusion criteria and compare demographic, psychiatric, and tobacco use characteristics of those who accept or decline enrollment. Another limitation, derived from the long-term follow up design, is loss to follow-up that could bias follow-up findings. We will perform an attrition analysis comparing characteristics of those followed to those not followed at each time point. In addition, to preserve statistical power needed to observe a 15% difference in the quit rate between conditions, we have increased the baseline sample size to accommodate an anticipated 20% loss to follow-up at 12 months. To increase follow-up data collection, clinicians will collect contact telephone numbers for the participant and at least two family members or caregivers. There is potential for underreporting of smoking status at follow-up. Participants reporting nonsmoking status at follow-up receive a reminder and a clinic appointment to complete exhaled CO testing.

If effective, this intervention could be included in the Catalan Health System and regularly offered to mental health patients who smoke, no matter their motivation to quit. We need to offer a wide range of possibilities to intervene in smoking cessation in this population as their smoking prevalence has not decreased in the last decade (Additional file 2).

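### The sample size of 334 + 167 does not follow from its stated inputs, and the control arm is given as both 167 and 176

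*Protocol article*

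**What the plan says.** The Sample size and randomization section gives the basis as "Setting a risk of α = 0.05 and β = 0.10, and with 2:1 randomization", with 20% abstinence expected in the intervention group (IG) and 5% in the control group (CG) at 12 months and an estimated 20% loss to follow-up. From this it concludes that "334 subjects are required in the IG arm and 167 in the CG arm to detect a statistically significant difference of 15 percentage points". The total is 501.

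The abstract lists the same rates, α, β and loss, but says the sample size "will be 334 participants (IG) and 176 participants (CG"). The Design section agrees with the abstract: "intervention group (*n* = 334) and control group (*n* = 176"). The total there is 510.

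The Discussion repeats the 15-point target. It says the baseline sample was enlarged for an anticipated 20% loss at 12 months "to preserve statistical power needed to observe a 15% difference in the quit rate between conditions".

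**The concern.** A contrast of 20% against 5% is large, and 501 participants looked too many for 90% power even after a 20% loss allowance. If the size does not follow from the inputs, at least one stated input is wrong, and a reader cannot tell what difference the trial was built to detect. That matters when the result is read. A true 10-point effect may have been within the design's reach, or it may lie below the stated target, depending on which figure is right.

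The two control-arm sizes raise a simpler problem: the recruitment target is 501 in one section and 510 in two others, and only one of them fits the stated allocation.

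**Working it through.** **Inputs** (Sample size and randomization): p_C = 0.05, p_I = 0.20, α = 0.05, power 0.90, k = IG/CG = 2, loss 20%. Sidedness is not stated, so two-sided is assumed (z = 1.960 and 1.2816) and one-sided is checked below.

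**1. Attempt to reproduce the stated size**

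Pooled-variance formula for the control arm:

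n_C = { z_α √[(1 + 1/k) p̄(1 − p̄)] + z_β √[p_C(1 − p_C) + p_I(1 − p_I)/k] }² / (p_I − p_C)²

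- p̄ = (0.05 + 2 × 0.20)/3 = 0.15
- First term: 1.960 × √(1.5 × 0.15 × 0.85) = 0.857
- Second term: 1.2816 × √(0.0475 + 0.08) = 0.458
- n_C = (1.315/0.15)² = 76.8, so 77; n_I = 153.6, so 154
- Dividing by 0.8: 77/0.8 = 96.25, so 97; 154/0.8 = 192.5, so 193. Total **290**.

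Other methods for the same 20% against 5%, divided by 0.8 and unrounded:

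| Method | CG | IG |
|---|---|---|
| Pooled | 96.0 | 192.1 |
| Continuity-corrected | 108.2 | 216.3 |
| Arcsine | 86.9 | 173.7 |
| Unpooled variance | 74.4 | 148.9 |
| Continuity-corrected, 95% power | 128.1 | 256.2 |
| **Stated** | **167** | **334** |

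The continuity-corrected row rounds up to 109 + 217 = 326. A one-sided test lowers the need (pooled n_C = 61.6 before the loss allowance). None of these reaches 167 and 334.

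**2. Power of the stated size at the stated effect**

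After 20% loss, 334 and 167 become about 267 and 134.

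- Null standard error: √[0.15 × 0.85 × (1/134 + 1/267)] = 0.0378
- Alternative standard error: √(0.0475/134 + 0.16/267) = 0.0309
- Power = Φ[(0.15 − 1.960 × 0.0378)/0.0309] = Φ(2.46) = **99.3%**

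With no loss (334/167) it is 99.9%. If the 20% lost are counted as smokers (16% against 4% on 334/167, an assumption about how intention to treat is applied), it is 99.1%.

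**3. What effect does the stated size fit?**

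With 267/134 followed and 90% power, the detectable difference above a 5% control rate is about 10.4 points. The arcsine formula for 15% against 5% gives:

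- h = 2 arcsin√0.15 − 2 arcsin√0.05 = 0.3444
- n_C = (1.960 + 1.2816)² × 1.5/0.3444² = 132.9, so 133
- 133/0.8 = 166.25, so **167**; 2 × 167 = **334**

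For the same rates, an unweighted mean rate in the pooled formula gives 165/330, while the usual weighted version gives about 180/360. At 15% against 5% with 267/134 followed, power is about 88% by the pooled normal approximation and 90% by arcsine.

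**4. Control arm**

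| Section | IG | CG | Total | Ratio |
|---|---|---|---|---|
| Sample size and randomization | 334 | 167 | 501 | 2.00:1 |
| Abstract; Design | 334 | 176 | 510 | 1.90:1 |

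Only 167 agrees with 2:1.

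**The case against.** The strongest reply has three parts.

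First, the 10-point explanation comes from searching over formulas. It is exact for one pair of rates, one formula and one order of rounding; unrounded arcsine gives 166.1/332.3, and the weighted pooled formula gives about 180/360. The article never mentions 15% abstinence or a 10-point difference, while the 15-point target appears in the abstract, the sample size section and the Discussion. This stands: a 10-point design is a plausible inference and not an established fact, and only the team knows which inputs were used. The error does not depend on it, because 334/167 fails for 15 points whatever its origin.

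Second, the mistake is in the safe direction. Power for the stated effect is higher than claimed, enrolment need not change, and the 167/176 difference is nine people, probably transposed digits. All of that is true and limits the harm. It does not make the statement correct: the article says 334 and 167 are required for a contrast that needs far fewer.

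Third, the excess might be a further loss allowance, or might serve the subgroup analyses that the Discussion says a large sample will permit. The article supports neither reading. The 20% loss is already in the stated figure, and the sample size section ties 334 and 167 to the 15-point contrast alone.

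**Conclusion.** Both parts hold. With 20% against 5%, two-sided α = 0.05, 90% power, 2:1 allocation and 20% loss, the trial needs about 290 randomized (326 with continuity correction). The stated 501 exceeds 290 by 211, and 211/290 = 73%. Its power at the stated effect is about 99.3% after loss, against the 90% stated. These figures assume a two-sided comparison of two proportions; a one-sided test would widen the gap.

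The control arm is 167 in one section and 176 in two, a difference of nine, and only 167 is consistent with 2:1.

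The trial is not underpowered for its stated target. The fault is that its account of what it was sized to detect, and of how many controls it will recruit, is wrong as written.

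**What to change.** 1. Use one control figure in the abstract, the Design section and the Sample size section: 167 (total 501) if 2:1 allocation is kept. If 176 (total 510) was intended, the 2:1 statement has to be corrected.
2. Go back to the calculation actually run and restate it as one true pair of effect and power, naming the formula. If the design difference was 10 points, that is 15% against 5% with about 90% power by arcsine (about 88% by the pooled normal approximation). If 20% against 5% is the real assumption, say that 334/167 gives about 99% power after 20% loss, and do not call that number required for 90%.
3. Bring the Discussion sentence on the 15-point difference into line with whichever statement is true.

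The cost is wording in four places. The stated detectable difference or the stated power changes; no participants are added or removed on account of the calculation.
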